## Exclusion criteria

- visible small palpebral fissure
- inflammatory bacterial diseases a causal factor for epithelial defects
- participation of the patient in another clinical trial within the last 4 weeks prior to the inclusion
- addiction or other diseases which do not allow the person concerned to evaluate the nature, scope and possible consequences of the therapeutic trial
- women who are either pregnant or breast feeding
- women of child-bearing age, except women who meet the following criteria:
  - post-menopausal (12 months natural amenorrhoe or 6 months amenorrhoe with serum FSH > 40 mIU/ml)
  - post-operative (6 weeks after bilateral ovariectomy with or without hysterectomy)
  - regular and correct application of a contraceptive method with an error rate < 7 % per year (eg implants, depot syringes, oral contraceptiva, intrauterine device – IUD). It should be considered that the combined oral contraception – as opposed to purely progesterone preparations – has a failure rate of < 1 %. Hormone coils with a Pearl index < 1 % are safer than copper coils.
  - sexual abstinence
  - vasectomy of the partner
- evidence that the patient presumably does not comply with the trial plan (e.g. lack of cooperation)

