**Inclusion criteria**

- male and female patients between 18 and 85 years
- epithelial defects of the cornea of different genesis (eg after injury, after acid burns, in autoimmune diseases such as rheumatoid arthritis)
- incipient corneal ulcer, unless there is no bacterial infection
- existence of the declaration of patient consent

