## Procedure of the clinical trial

### *Visit 1 (Screening Visit, Baseline)*

Each participating person has to be fully informed about the therapeutic trial before agreeing to participate in the therapeutic trial. The medical information and education is given personally by the investigating physician as well as in writing by the patient information sheet. Only subsequently to the clarification of all questions, the patient is asked to sign and to personally date two copies of the consent form. Afterwards, one copy of the patient information sheet / consent form is issued to the patient; the second copy shall be preserved in a document file at the trial centre.

The demographic data, anamnesis, and secondary diagnoses are acquired at the visit 1. In addition, an ophthalmological examination is carried out, and vital parameters as well as the body weight are

recorded. Among women of childbearing age, a pregnancy test will be performed. The patient will be enrolled in the therapeutic trial according to the results of verification of the inclusion exclusion criteria.

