### ***Visit 5 (day 7 postoperative, final visit)***

After one week, the amniotic membrane holder is removed and a final ophthalmological examination is performed. In addition, the subjective perception is recorded. In the strict sense, the trial is completed at this time.

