**Specialized information or investigator brochure (for non-approved drugs) is enclosed.**

### Risk-benefit assessment

Due to a good compatibility, the amniotic membrane does not provides any significant side effects, and the membrane is approved for medical use. Any potential side effect can only be of mechanical nature, such as the development of dents or pressure marks in the area of the con-junctiva. The investigation of these undesirable effects is - among other things - subject of this study.

The standard procedure is to suture the amniotic membranes onto the ocular surface, so that a definite and good standard is specified in this connection. The here described new method is merely a new form of application of an amniotic membrane.

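### The two eligibility lines on bacterial infection differ in scope, so an epithelial defect with a bacterial infection that did not cause it is barred by no listed criterion

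*Protocol*

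**What the plan says.** Infection appears twice in the eligibility criteria of the Protocol, section III.

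- **Exclusion criteria:** "inflammatory bacterial diseases a causal factor for epithelial defects". A word seems to be missing after the noun, but the sense is clear: bacterial disease that contributed to the defect.
- **Inclusion criteria, ulcer line:** "incipient corneal ulcer, unless there is no bacterial infection". Taken literally, this admits an ulcer only when bacterial infection is present. The apparent intent is the reverse.

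The other disease-related entry line is open as to cause: "epithelial defects of the cornea of different genesis". Injury, acid burns and autoimmune disease are given as examples only.

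Visit 1 makes the criteria decisive: "The patient will be enrolled in the therapeutic trial according to the results of verification of the inclusion exclusion criteria". At the same visit "an ophthalmological examination is carried out"; no rule on infection is attached to it.

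The Risk-benefit assessment states: "Any potential side effect can only be of mechanical nature". It names dents and pressure marks on the conjunctiva and does not mention infection.

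**The concern.** The protocol gives bacterial infection two different scopes without explaining why. On its apparent intent, the ulcer line turns on whether bacterial infection is present. The exclusion line turns on whether bacterial disease caused the defect. A burn that later becomes infected has a non-bacterial cause, so it passes the exclusion although the eye is infected when the holder is placed.

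Two things are at stake. The first is the enrolled population: the criteria allow in eyes whose risk the Risk-benefit assessment does not discuss. The second is interpretation. Success under Assessment of the effectiveness requires a week free of pain and discomfort, whatever the source. Section VI ends the trial if two of the first five patients fail to tolerate the holder, and it does not require that the holder be the reason. Symptoms of an infection already present would be read as incompatibility of the ring. The secondary target, improvement by the end of observation without a control group, could likewise reflect the course of the infection.

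**Working it through.** The protocol gives no figure on this point, so there is none to reproduce. The check sets the criteria side by side and runs each type of eye through them. It assumes that the epithelial-defect line and the ulcer line are alternative routes of entry, which the protocol does not state. The remaining criteria (age, consent, palpebral fissure and so on) are taken as met.

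| Eye at baseline | Inclusion criteria | Exclusion criteria | Result as written |
|---|---|---|---|
| A. Epithelial defect caused by bacterial disease | Meets the defect line | Excluded | Barred |
| B. Incipient ulcer, secondary bacterial infection | Literal text: admitted. Apparent intent: not admitted | Not excluded, because the infection is not the cause | Admitted on the literal text, barred on the intent |
| C. Burn or autoimmune defect, no ulcer, with secondary or concurrent bacterial infection | Meets the defect line | Not excluded, because the infection is not the cause | Not barred |
| D. Epithelial defect from active non-bacterial infection | Meets the defect line, since causes are open | Not excluded, because it is not bacterial | Not barred |

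**Step 1, bacterial infection.** Compare B on its apparent intent with C. In both, the bacterial infection is present but did not cause the lesion. B is kept out and C is not. Correcting the double negative would settle B but leave C unchanged, because the ulcer line does not reach epithelial defects without ulcer. Supplying the missing word in the exclusion would not remove its causal limit.

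**Step 2, non-bacterial infection.** No part of the protocol mentions it. Row D is therefore silence, not a contradiction between two passages.

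**Step 3, other safeguards.** The visit descriptions, Risk-benefit assessment and section VI contain no further eligibility rule on infection. Visit 1 collects history, secondary diagnoses and an eye examination, but enrolment follows the listed criteria.

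**Step 4, weight of one such eye.** Section III plans 10 patients. One patient is 1/10 = 10 percentage points of the success proportion. Under section VI, two non-tolerating patients among the first five end the trial. These figures apply to any patient; they show how little it takes in a sample of this size. They do not estimate how often infected eyes would be enrolled.

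**The case against.** The strongest reply is that the protocol is consistent about organisms: both lines speak only of bacteria, so its silence on other infections need not be an error. This stands. A reader might infer that the protocol treats infection in general as a reason not to place the holder, and that row D breaches its own rule. No section states such a principle, so for row D the documents support only a request for clarification.

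A reader might also infer that infected eyes will be enrolled. The text supports less: no listed criterion bars them. An investigator who sees infection at baseline may decline the patient, but the protocol gives no rule for doing so.

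A third tempting reading is that the ring would stay on an infected surface for a week, or up to 4 weeks, whatever happens. The documents do not support it. Section II says the holder can be taken out whenever needed. Checks are planned on days 1, 3 and 7, and Assessment of the effectiveness refers to daily visits. Longer observation depends on compatibility, and longer wear on individual assessment.

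Nor does the Risk-benefit assessment say that the eye must be uninfected. It discusses effects of the membrane and holder, and it can be faulted only for not addressing infection.

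Finally, the success criterion attributes pain to no cause in any patient, so the scoring weakness is not specific to infection. That is true; the scope gap adds one avoidable source of it.

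None of these replies explains the difference between rows B and C.

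**Conclusion.** The point holds in this form: the two statements on bacterial infection differ in scope. As written, an epithelial defect of another cause with secondary or concurrent bacterial infection is barred by no listed criterion. The same is true of a defect from active non-bacterial infection, but there the protocol is silent and does not contradict itself.

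The effect on the trial is potential and its size unknown, because the protocol gives no expected number of such eyes. It could matter because the sample is small and neither the pain component of the endpoint nor the tolerance rule asks for the cause.

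The conclusion rests on two assumptions: that the ulcer line was meant to bar bacterial infection, and that the defect and ulcer lines are alternative routes of entry. If the ulcer line is taken literally instead, the conflict with the exclusion is sharper, since one line would then require what the other partly excludes.

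**What to change.** 1. Reconcile the ulcer line under Inclusion criteria with the infection line under Exclusion criteria. Bacterial infection of the study eye should have one scope for ulcers and epithelial defects and should not depend on its having caused the defect. Correct the double negative in the same edit.
2. State that the criterion is checked at the ophthalmological examination already planned for Visit 1.
3. Have the sponsor state whether active non-bacterial infection is excluded. If it is not, the Risk-benefit assessment should address it. Which organisms to exclude is for the sponsor to decide.

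The cost is a reworded pair of eligibility lines and, at most, a short addition to the Risk-benefit assessment. No visit or examination is added. The small downside is that a few infected eyes are deferred or not enrolled.

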## Procedure of the clinical trial

### *Visit 1 (Screening Visit, Baseline)*

Each participating person has to be fully informed about the therapeutic trial before agreeing to participate in the therapeutic trial. The medical information and education is given personally by the investigating physician as well as in writing by the patient information sheet. Only subsequently to the clarification of all questions, the patient is asked to sign and to personally date two copies of the consent form. Afterwards, one copy of the patient information sheet / consent form is issued to the patient; the second copy shall be preserved in a document file at the trial centre.

The demographic data, anamnesis, and secondary diagnoses are acquired at the visit 1. In addition, an ophthalmological examination is carried out, and vital parameters as well as the body weight are

recorded. Among women of childbearing age, a pregnancy test will be performed. The patient will be enrolled in the therapeutic trial according to the results of verification of the inclusion exclusion criteria.

### ***Visit 2 (OP-day)***

Application of the amniotic membrane holder AmnioClip on the ocular surface.

### ***Visit 3 and 4 (day 1 and 3 postoperative)***

Verification of the position of the amniotic membrane holder AmnioClip, inspection of the eye, questions concerning pain and subjective well being. Photodocumentation.

### ***Visit 5 (day 7 postoperative, final visit)***

After one week, the amniotic membrane holder is removed and a final ophthalmological examination is performed. In addition, the subjective perception is recorded. In the strict sense, the trial is completed at this time.

### ***Following visits (day 8 to 30)***

Depending on the individual assessment, the amniotic membrane holder may be left on the cornea for more than 1 week. In this case, a final visit will be performed at a later time, but at least after 4 weeks. At this visit, the holder is removed permanently, and there is a clinical slit lamp examination.

### **Assessment of the effectiveness**

The assessment of effectiveness is performed by daily visit of the probands and by assessment of the anterior eye segment. The primary key performance target of the trial refers to the compatibility of the developed amniotic membrane holder.

If the following points are applicable for one week:

- complete eyelid closure is possible,
- ring does not touch the cornea,
- amniotic membrane is clamped firmly in the holder and is located on the cornea,
- no pain or discomfort occurs,

then this will be considered as a success.

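### The protocol bases primary success over one week on daily visits but schedules postoperative visits only on days 1, 3 and 7, so failures that resolve between visits and go unreported may be scored as successes

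*Protocol*

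**What the plan says.** The Protocol section Assessment of the effectiveness states how the primary endpoint is observed: "The assessment of effectiveness is performed by daily visit of the probands and by assessment of the anterior eye segment". It then defines success by four conditions, introduced with "If the following points are applicable for one week". In short, the lids close fully, the ring stays clear of the cornea, the membrane is held firmly and lies on the cornea, and "no pain or discomfort occurs".

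The procedure of the trial sets out the visits one by one. After the day of application they are:

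- "Visit 3 and 4 (day 1 and 3 postoperative"), with this content: "Verification of the position of the amniotic membrane holder AmnioClip, inspection of the eye, questions concerning pain and subjective well being", plus photographs.
- "Visit 5 (day 7 postoperative, final visit"), with this content: "After one week, the amniotic membrane holder is removed and a final ophthalmological examination is performed. In addition, the subjective perception is recorded".

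The section Following visits allows the holder to stay in place beyond one week in individual cases, with a later final visit. No diary, telephone contact or other observation is listed for days 2, 4, 5 and 6.

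**The concern.** An endpoint that must hold throughout a week needs a stated source of information for the whole week. The protocol gives two sources that do not agree: a daily visit in the endpoint section, and three postoperative visits in the schedule. A site cannot tell from the document which to follow, and a reader of the results cannot tell what a success means.

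The listed visit content adds to the doubt. Complete eyelid closure, one of the four conditions, is not named at any visit. Visit 5 mentions removal before the examination and names no check with the holder in place, although lid closure over the ring, ring-to-cornea contact and firm clamping can be judged only while it is there.

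The study has 10 patients and no control group, so each misclassified patient moves the success rate by 10 percentage points. Missed failures can only raise that rate.

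**Working it through.** The protocol states no expected success rate, power or derivation of the 10 patients, so there is no figure of its own to reproduce. The check is a count of observed days, followed by an illustration of what the gap could do.

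**Coverage.** The endpoint spans postoperative days 1 to 7. Daily visits would give 7 assessments. The schedule gives days 1, 3 and 7, so coverage is 3/7 = 43%. Days 2, 4, 5 and 6 (4/7 = 57%) have no listed observation, and the longest gap is days 4 to 6.

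**Lower bound.** If every failure either persists until the next visit or is reported there, and is recorded, the three visits find all of them. The bias is 0.

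**Illustration A.** Assumptions, none of them from the protocol: a share f of patients each has exactly one failing day, equally likely to be any of days 1 to 7; the failure lasts only that day; the patient does not report it later. It is seen with probability 3/7 and missed with probability 4/7.

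Observed success = (1 − f) + f × 4/7

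| f | True success | Observed success |
|---|---|---|
| 0.20 | 80% | 0.80 + 0.20 × 4/7 = 91.4% |
| 0.40 | 60% | 0.60 + 0.40 × 4/7 = 82.9% |
| 0.60 | 40% | 0.40 + 0.60 × 4/7 = 74.3% |

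**Illustration B.** A second model tests whether the result hangs on the one-day form. Assume a probability q of failure on each day, independent between days, each failure lasting only that day and not reported later. Success is (1 − q)^7 if all seven days are seen and (1 − q)^3 if three are.

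| q | Seen daily | Seen on days 1, 3, 7 | Difference (points) |
|---|---|---|---|
| 0.01 | 93.2% | 97.0% | 3.8 |
| 0.02 | 86.8% | 94.1% | 7.3 |
| 0.05 | 69.8% | 85.7% | 15.9 |
| 0.10 | 47.8% | 72.9% | 25.1 |

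In 10 patients this is between about 0.4 and 2.5 extra apparent successes. Both models describe the unfavourable end, because both assume that nothing persists and nothing is recalled.

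**The case against.** The strongest reply is that the gap may not exist or may not matter. If the daily visit is the operative statement, every day is seen. If the three-visit schedule is operative, a displaced ring or loosened membrane that stays so would be found on day 3 or day 7. Pain can be reported when the patient is asked on days 1 and 3, or when perception is recorded on day 7. Holder position and pain are named outright at Visits 3 and 4, and lid closure or corneal touch could fall under inspection of the eye. Much of this stands, and it limits the concern to failures that are both transient and unreported. It does not remove the contradiction. Nor does the protocol say that the questions cover the days since the last visit. A statistical analysis plan could not repair this, because it cannot recover observations that were never made.

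A reader might infer three stronger things that the document does not support:

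- That failures between visits are counted as successes. No section says how an unobserved day is scored.
- That the endpoint cannot be determined at all, or that nobody looks at the ring before taking it out. The order of words in the Visit 5 sentence is not proof of a strict sequence, and removal on day 7 is not universal, since longer wear is allowed.
- That the early stopping rule is weakened by a known amount. That rule refers to two of the first five patients not tolerating the holder and is not tied to the four-condition definition.

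**Conclusion.** The contradiction is plain on the face of the protocol and concerns the primary endpoint: daily assessment in one section, 3 of 7 days in another. It should be settled before the results are read as a success rate for the whole week.

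The consequence is conditional. Under the three-visit schedule, failures that resolve between visits and are not reported, such as a brief lid-closure problem, corneal touch or membrane shift, may be scored as successes, and any such error favours the device. The size runs from zero, if failures persist or are reported, to about 11, 23 or 34 percentage points (91.4 − 80, 82.9 − 60, 74.3 − 40) if 20%, 40% or 60% of patients each have one unreported one-day failure. Those shares are assumptions. The protocol gives no basis for choosing among them.

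**What to change.** 1. Reconcile Assessment of the effectiveness with the sections for Visits 3, 4 and 5. State which days, and which sources (examination, patient report), establish that each condition held for the week. Which visit frequency applies is for the investigators to decide.
2. Record the four success conditions, including eyelid closure, as yes/no items at every postoperative visit that is kept. On day 7, complete them with the holder still in place, before any removal; this also covers patients whose holder stays in longer.
3. If visits are not daily, choose one of two definitions. Either add a one-line daily patient diary (pain, discomfort, holder displaced) and define success as all four conditions met at every visit with no failing diary day, or define success as all four conditions met at days 1, 3 and 7 and drop the claim to the whole week.

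The cost is protocol wording, a one-page form and, if chosen, a short diary for 10 patients. The observed success rate may come out lower.

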The proposed project is acceptable from an ethical point of view, since it is already known that large contact lenses or scleral shells are compatible on the eye surface. The insetion of the amniotic membrane holder AmnioClip into the palpebral fissure can be controlled by means of a slit-lamp examination. The removal of the amniotic holder AmnioClip is possible at any time without problems. This is where the clinical relevance of the pilot study comes to the fore. A ring covered with an amnion which is placed as a contact lens on the eye may be inserted or removed at any time without any surgical effort.

Together with the spanned amniotic membrane, the amniotic membrane holder can be distributed by eye banks or companies to hospitals or surgeries.

The observation of a placebo group is not necessary, because suturing of an amniotic membrane has been enforced through many trials and observations against an ointment therapy.

Aim of the project:

The primary objective of this project is to examine the mounting and compatibility of the amniotic membrane holder including the amniotic membrane (AmnioClip) in the eye of the patient.

The secondary objective of the study is to examine to what extent the underlying disease can be improved during the observation period (1 week). This is done without a control group.

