**6. Procedure of the clinical trial see III****III. Questions to patients and probands**

10 persons are involved in the pilot study.

It is planned to involve the patients starting Feb 2011.

The postoperative observation period amounts one week. Dependent upon compatibility, the postoperative observation period may be extended to 4 weeks.

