## **VI. Interim analysis and criteria for discontinuation**

The therapeutic trial will be finished prematurely, if:

- two of the first five patients do not tolerate the amniotic holder,
- the rate of patient recruitment is inadequate,
- serious, unresolvable problems concerning the quality of the captured data occur,
- unforeseen circumstances occur which do not allow a continuation of the therapeutic trial,
- unacceptable risks and toxicities occur (decision in accordance with a performed new benefit-risk assessment),
- new scientific results during the term of the therapeutic trial do not permit to continue with this therapeutic trial.

The LKP decides on the discontinuation of the clinical trial.

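### The pain point of the success definition is absolute and no pain value is named before placement, so disease pain can be counted against the holder

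*Protocol*

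**What the plan says.** The question is about the device. Protocol section II.1 states: "The primary objective of this project is to examine the mounting and compatibility of the amniotic membrane holder" together with its membrane. The design is small and uncontrolled. Section III gives the size: "10 persons are involved in the pilot study". In section II.5 the box for an open study is ticked and the box for a comparative one is not. Of the secondary objective, section II.1 says: "This is done without a control group".

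Under *Assessment of the effectiveness*, a patient is a success if four points hold for a week: full lid closure, no contact between ring and cornea, a membrane firmly clamped and lying on the cornea, and "no pain or discomfort occurs". The fourth point carries no grade, no comparison with an earlier state and no requirement that the holder be the cause.

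The *Inclusion criteria* admit "epithelial defects of the cornea of different genesis", with injury, acid burns and autoimmune disease as examples, and also incipient ulcers.

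For baseline the protocol says: "The demographic data, anamnesis, and secondary diagnoses are acquired at the visit 1". It adds an eye examination, vital parameters, weight and, where relevant, a pregnancy test. Visit 2 lists only the placement. Visits 3 and 4, on days 1 and 3, are the first to list "questions concerning pain and subjective well being". Visit 5 on day 7 records subjective perception.

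Section VI ends the trial early if "two of the first five patients do not tolerate the amniotic holder". It does not define tolerance or refer back to the four success points.

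**The concern.** The endpoint is meant to show whether the eye accepts the holder. Its fourth point, as worded, asks whether the eye is free of pain and discomfort from any cause. In patients with an open corneal surface these can differ. A patient whose eye hurt before placement, and hurts equally or less afterwards, can be recorded as a failure of the holder.

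A control arm or a pre-placement value would help to tell the two sources apart. The design has no control arm and the visit schedule names no pre-placement pain value. The success proportion would then depend on which diseases happened to be enrolled, even with an identical device. A value not collected before placement cannot be recovered later by any analysis plan.

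**Working it through.** **Plan's own figure.** There is none to reproduce. The protocol states no target success rate, no rate of disease pain and no rate of device-caused pain.

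**Pain items by visit**

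| Visit | Timing | Pain or comfort item named |
|---|---|---|
| 1 | baseline | none |
| 2 | placement | none |
| 3, 4 | days 1 and 3 | pain and well-being questions |
| 5 | day 7 | subjective perception |

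Every named item falls after placement.

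**Inputs for the size (assumptions).** Let d be the probability that the holder itself causes pain or discomfort in the week, and b the probability of disease discomfort in the week whatever the device does. The two are taken as independent.

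**Formula.** P(pain point met) = (1 − d)(1 − b). If only device-caused pain counted, it would be 1 − d. The absolute wording therefore multiplies the proportion by (1 − b).

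| b | d = 0 | d = 10% | expected failures of 10 at d = 0 |
|---|---|---|---|
| 0 | 100% | 0.90 × 1.00 = 90% | 0 |
| 10% | 90% | 0.90 × 0.90 = 81% | 1 |
| 20% | 80% | 0.90 × 0.80 = 72% | 2 |
| 50% | 50% | 0.90 × 0.50 = 45% | 5 |

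All four points must hold, so overall success cannot exceed these values.

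**At least one false failure.** With d = 0 and ten patients, the chance that at least one fails on disease pain alone is 1 − (1 − b)^10. This is 1 − 0.9^10 = 65% at b = 10% and 1 − 0.8^10 = 89% at b = 20%.

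**Why the result cannot be disentangled afterwards.** An expected proportion of 72% arises from d = 10% with b = 20%, from d = 28% with b = 0, and from d = 0 with b = 28%. These describe very different devices, and the data as scheduled cannot choose among them.

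**The case against.** **The point may mean new pain.** The verb *occurs* allows this. The list follows a sentence confining the target to compatibility of the holder, and section II.1 expects the device not to cause pain after placement. This stands in part: the text does not say that pre-existing pain must be scored as failure. But new pain cannot be recognised reliably without a recorded earlier state, so this reading needs the same missing value.

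**History-taking or the eye examination may pick up pain.** Possibly. No pain item is specified there, nothing makes it comparable with the later questions, and the criterion refers to no baseline.

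**A strict criterion is conservative.** True. As written, the error runs against the device and cannot create a false claim of compatibility. It can still understate compatibility by an unknown amount.

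**Only one of four points is affected.** Also true. Ring contact and clamping are mechanical and lid closure is a matter of fit. A reader might infer that the whole endpoint is uninterpretable; the documents do not support that.

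**The stopping rule.** A reader might infer that disease pain would stop the trial. If every such pain counted as non-tolerance, a perfectly tolerated holder at b = 20% would meet the two-of-five condition with probability 1 − 0.8^5 − 5 × 0.2 × 0.8^4 = 26%. The documents do not support using this as a finding. Section VI makes the holder the object of non-tolerance, never refers to the success points, and leaves the decision to the lead investigator. A stopping rule and a success criterion may also use different standards. What remains is that the relation between the two is unstated.

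**Conclusion.** The concern holds for the fourth success point. Its wording is absolute, no pain value is named before placement, and there is no control arm. Disease pain can therefore be scored as device failure, and a new-onset reading cannot be applied reliably.

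The direction is against the holder and the size is unknown. On assumed, independent disease discomfort of 10%, 20% or 50%, a perfectly tolerated holder would meet the point in 90%, 80% or 50% of patients. At b = 0 there is no loss. The protocol does not say how many patients have pain at entry, so these figures show sensitivity and are not predictions.

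Early stopping on disease pain is not established. Section VI raises only a question of reconciliation.

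**What to change.** 1. Ask one pain and comfort question, on one simple scale, at Visit 1 and again at Visit 2 before the anaesthetic drop and placement. Use the same question at every later visit.
2. Define the fourth point as no new and no worsened pain or discomfort against the pre-placement value during the week.
3. Report absolute pain values, and the proportion with no pain at all, descriptively.
4. Report the four success points separately as well as together.
5. State how non-tolerance in section VI relates to the four success points, so that the two passages are reconciled. No stopping definition is proposed here.

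**Cost.** One extra question at two existing visits and a reworded criterion.

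**Downside.** A patient with severe pain at baseline can hardly worsen. Without a control arm, worsening may be disease progression, and unchanged pain may be device pain replacing resolving disease pain, which the revised point would count as success. Change from baseline thus reduces the mixing of device and disease but does not remove it, which is why the absolute values must be shown too.
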